### 5.3.3 Informed consent

Study personnel will conduct the informed consent discussion with the parent(s) or guardian(s) of children and with the other adult respondents. Informed consent will be conducted in the appropriate language and a translator will be used if necessary. Consent forms will be available in English and the local languages. Following the informed consent discussion, parents/guardians will be asked by the study personnel to sign a written consent form for their children to participate in a research study (appendix 3) and a second approved consent form for the future use of biological specimens obtained during the course of the study (appendix 4). If the parent/guardian is unable to read or write, their fingerprint will substitute for a signature, and a signature from a witness to the informed consent procedures will be obtained. Written assent to participate in the study will also be obtained from children aged 8 years and older at the time of screening (appendix 5). Respondents aged 18 years and older will be asked by the study personnel to sign a written consent form to participate in a research study (appendix 3) and a second approved consent form for the future use of biological specimens obtained during the course of the study (appendix 4). If the respondent is unable to read or write, their fingerprint will substitute for a signature, and a signature from a witness to the informed consent procedures will be obtained

### 5.3.4 Clinical survey procedures

The clinical surveys will include a fingerprick blood sample for measurement of hemoglobin, thick and thin blood smear, rapid diagnostic test (RDT) for malaria, and filter paper blood sample. All children under 15 years will have a fingerprick blood sample taken for measurement of hemoglobin, thick and thin blood smear, rapid diagnostic test (RDT) for malaria, and filter paper blood sample. One person randomly selected in each of the age category 15-24 years, 25-34 years, 35-44 years, 45-54 years, and > 55 years shall have a fingerprick blood sample taken for measurement of hemoglobin, thick and thin blood smear, rapid diagnostic test (RDT) for malaria, and filter paper blood sample.

### 5.3.5 Clinical management

Respondents who are tested with an RDT and test positive for malaria shall be offered treatment for malaria in their homes. Respondents with a positive RDT and no evidence of severe malaria will be treated with artemether-lumefantrine, the standard national regimen. Respondents with a positive RDT and evidence of danger signs of severe disease will be referred to the nearest health facility for further evaluation and treatment. Respondents with a hemoglobin level of < 5.0 g/dL will be referred to the nearest health facility for further evaluation and transfusion. Any respondent with other concerning clinical symptoms will also be referred to an appropriate health care facility at the discretion of the study personnel.

## 6.0 SCHOOL SURVEYS

## **6.1 Overview.**

Surveys will be conducted in three schools per site which will be randomly selected from a list of all primary schools in the sub-county generated during an enumeration exercise which has already been completed as part of a separate protocol. The surveys will be done twice a year (once during the rainy season and once during the dry season). New lists of three schools will be randomly generated for each survey using replacement; as a result the same school may participate in the survey more than once.

## 6.2 Selection criteria

Children enrolled in participating schools will be assessed for the following eligibility criteria:

**Inclusion criteria**

1. Aged ≥ 6 to < 15 years
2. Student enrolled at participating school in classes 2 to 6
3. Student has lived in the sub-county for the last six months
4. Provision of informed consent from parent or guardian
5. Provision of assent by student

## 6.3. Initial recruitment and consent

Schools in the participating sub-counties will be selected using simple random sampling from a list of all primary schools in the sub-county generated during the enumeration exercise. Prior to the day of the survey, staff from participating schools will be sensitized about the study and plans for recruitment. A random sample of 150 children aged 6-15 years will be selected from each school using the school register. Thirty children will be randomly selected from each of the classes 2-6 in the selected schools to participate in the study. The parents/guardians of selected children will be invited to the school for a meeting with the study teams, to review the selection criteria for study participation and to gain informed consent. During the meetings, the purpose and procedures of the study will be discussed, informed consent forms will be distributed (appendix 6), and written informed consent will be sought from the parents/guardians. Those parents who do not attend the school meetings will be visited at home and the consent will be sought from their homes. Consent forms will be made available in the local languages and in English. Consent to take part in the research study (appendix 6) and consent for future use of biological specimens (appendix 7) will be sought. Details about the location of the students’ homes will also be obtained from the parent/guardians to facilitate tracing in the event the child is selected for household mapping.

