A complementary, inexpensive framework for malaria planning, monitoring and evaluation is offered by school malaria surveys (12-14). The practical advantages of sampling children at school are clear: identification and selection of individuals is simplified, compliance is high, and costs are reduced, since only a fraction of the population is examined. In addition, ministries of education are increasingly developing or upgrading national school databases using geographical information systems (GIS). This allows incorporation of information on school locations and enrolment into a single database, and the use of geo-statistical methods to model risks between schools and across un-sampled schools. There are also important epidemiological reasons for sampling children who attend school. Historically, malaria endemicity was defined on the basis of PR among children aged 2-10 years, and geographical reconnaissance of malaria was recommended in all areas prior to a control program launching into an attack phase of the Global Malaria Elimination Program (15). Recent mathematical models of malaria transmission dynamics indicate that EIR determines both the rate at which PR rises during early childhood and the age at which maximum PR is attained (16). Age-stratified studies in varying transmission settings reveal that PR consistency has a convex relationship with age, with PR rapidly rising among young children, attaining a maximum within the 5-10 year old age class, and declining among adolescents and young adults, thereafter maintaining a relatively stable low value throughout adulthood (17). Such consistency in the relationship between PR and age permits age-standardization of available PR estimates to the 2 to 10 year age range on the basis of catalytic conversion models (17), although estimates are most precise when the majority of the sampled population are within this age range.

The Uganda Malaria Surveillance Project (UMSP) is implementing routine surveillance of outpatient monthly malaria cases, laboratory confirmed suspected malaria cases, the prescription practices of health workers and anti-malarial drug usage at six sites across the country.

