## 5.1 Household survey

### 5.1.1 Selection of households

A sample of 200 residential households will be selected in each site. In order to create a sampling frame for the selection of participating households, all residential households within each of the three sites have been enumerated and mapped prior to the onset of the surveys as part of a separate protocol. A random sample of households will be selected from each site using computer-generated random numbers to generate a list of households to be approached. Study personnel will conduct door-to-door recruitment to identify those households with at least one adult household resident in sequential order according to the recruitment list. Households without a child of appropriate age will be removed from the recruitment list. Residents not home during the initial contact will be re-visited on at least three other occasions before eliminating them from our sample selection process. New recruitment lists will be randomly generated for each survey using replacement.

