## 8.2 Analytical plan and sample size/power calculations

Statistical analysis will be undertaken using Stata 10 (Stata Corp., College Station, TX, USA). The prevalence of malaria infection will be based on the thin and thick blood smear readings. This procedure will enable estimation of parasite density, differentiation of Plasmodium species and identification of gametocytes. The proportion of children infected with single and multiple parasite species and the mean intensity of infection/parasite density will be calculated. Differences in proportions by age, sex and transmission setting will be assessed by logistic regression and differences in means using a Student t-test (for parametric data) and a Mann-Whitney test (for non-parametric data). Prevalence of infection and anemia, and coverage rates will be presented as frequencies with appropriate 95% binomial confidence intervals. The report and other related documents will be extensively disseminated to stakeholders. Avenues for dissemination will include publications, working papers, and atlases.

Infection. The primary metric used to measure infection for both the gold standard method (community surveys) and streamlined method (school surveys) will be the parasite rate (PR), defined as the number of positive blood smears divided by the number of smears examined. For the gold standard method, PR will be measured using the cross-sectional surveys of an estimated 300 children (200 households x 1.5 children per household) aged 6-14 years from the community surveys. For the streamlined method, PR will be estimated using cross-sectional surveys of 300 children (3 schools x 100 children per school) aged 6-14 years from the primary school surveys.

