We will test the hypothesis that estimates of PR will be similar using the two methodologies. Point estimates of PR will be calculated for each biannual survey and compared using the McNemar’s test of paired proportions. Assuming that we will have a sample size of 300 children per survey for each methodology, we will have 80% power (one-sided significance level of 0.05) to reject the alternative hypothesis that there is a difference in estimates of PR assuming that the absolute difference in PR is no greater than 10% across a range of PRs in the community surveys of 20-80%. Whether or not these analyses show any evidence of significant differences between the methods, we will explore whether there is any systematic bias in the estimate of the streamlined method compared to the gold standard method (e.g. the streamlined method consistently over- or underestimates PR). Ecological logistic regression models will be used to predict the result of the gold standard method using data from the streamlined method, allowing adjustment for bias. Final models will then be prospectively validated in independent test sets to insure their accuracy.

Mortality. The primary metric for malaria mortality will be the relative change in absolute measures of malaria mortality. For the gold standard method, the measure of malaria morality will be the number of malaria-associated deaths in children under 5 years of age per 1,000 live births. Data on malaria mortality using the gold standard method will come from the biannual community surveys and verbal autopsy. For the streamlined method, the measure of malaria morality will be the number of malaria-associated deaths in children under 5 years of age captured by our inpatient surveillance system (described in another protocol).

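### Drawing only three schools per site by simple random sampling leaves their geographic spread to chance, adding avoidable random error to each survey's school-community comparison if parasite rate varies within the sub-county

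*Protocol*

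**What the plan says.** School arm. Protocol section 6.1 has the schools "randomly selected from a list of all primary schools in the sub-county generated during an enumeration exercise", and adds: "New lists of three schools will be randomly generated for each survey using replacement". Section 6.3 names the method: "Schools in the participating sub-counties will be selected using simple random sampling from a list of all primary schools in the sub-county". Neither section mentions strata, zones or sorting by area.

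Community arm. Section 5.1.1 states: "A random sample of households will be selected from each site using computer-generated random numbers". It also states that "all residential households within each of the three sites have been enumerated and mapped prior to the onset of the surveys". Location is therefore known for households, but it is not used in the draw.

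Comparison. Section 8.2 sets the school sample at "300 children (3 schools x 100 children per school"), against an estimated 300 community children of the same ages. It continues: "Point estimates of PR will be calculated for each biannual survey and compared". The power statement uses a 10-point absolute difference.

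Place. Section 1.3 names, among the attractions of school databases with locations, the "use of geo-statistical methods to model risks between schools". Section 6.6 maps the homes of 20% of selected pupils, but only after selection and only to describe where pupils live.

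**The concern.** Each survey sets pupils from three schools against children from 200 households spread over the whole sub-county. The households cover the area almost automatically; three schools need not. If transmission is uneven within the sub-county, part of any measured difference reflects where the three schools lay and not how the school method performs.

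Objective 2 rests on these differences. Section 8.2 makes the comparison survey by survey, and section 4.1 commits to two surveys a year for at least two years, so only four per site are guaranteed. Section 8.2 also uses school results to predict community results by regression. Random error in the predictor weakens that fitted relation, and redrawing schools at each round does not undo this.

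**Working it through.** **The plan's own figure.** With 300 independent children per arm, PR 50%, a 10-point difference and one-sided alpha 0.05: SE = √(2 × 0.25/300) = 0.0408, and power = Φ(0.10/0.0408 − 1.645) = 0.79. The stated 80% is reproduced to within about a point as a worst case. It contains no term for school or place.

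**Inputs from the protocol.** Three schools of 100 pupils; about 300 community children; 200 households; a 10-point difference.

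**Assumed inputs (the protocol gives none of these).** Three zones with equal numbers of schools; 12 schools; mean PR 50%; school SD within a zone 5 points; pupils live in their school's zone; no true difference between methods; no household clustering.

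**Step 1: coverage.** With N schools, P(at least one zone has no school) = 1 − (N/3)³ / C(N,3).

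| N | 6 | 9 | 12 | 15 | 30 | 60 |
|---|---|---|---|---|---|---|
| P | 60% | 68% | 71% | 73% | 75% | 77% |

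For N = 12: 1 − 64/220 = 0.71.

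**Step 2: SD of the difference, adjacent zones 10 points apart (40/50/60%).** Variance components in points²:
- Zone part under simple random sampling: (1 − 3/12) × (66.67 × 12/11)/3 = 18.18. With one school per zone it is 0.
- School part within zones: (1 − 1/4) × 25/3 = 6.25 if the community PR is the average over the listed schools' areas (A), or 25/3 = 8.33 if it is fixed by zone alone (B).
- Pupils: (2500 − 66.67 − 25)/300 = 8.03.
- Community children: 2500/300 = 8.33. With households also stratified: (2500 − 66.67)/300 = 8.11.

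| | As planned | Schools spread | Schools and households spread |
|---|---|---|---|
| A | √40.79 = 6.4 | √22.61 = 4.8 | √22.39 = 4.7 |
| B | √42.87 = 6.5 | √24.69 = 5.0 | √24.47 = 4.9 |

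By the normal approximation, an apparent difference beyond 10 points occurs in about 12-13% of surveys as planned and 3-4% with spread schools.

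**Step 3: smaller gaps.** At 5 points the zone part is 0.25 × 16.67 × 12/11 = 4.55 and the pupil part 8.19. The SD goes from 5.2 (A) or 5.4 (B) to 4.8 or 5.0. At zero gap it is 4.8 (A) or 5.0 (B) either way.

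**Step 4: pupils from other zones.** If 30% of pupils live evenly in the other two zones, a 10-point gap between zones becomes 0.70 × 10 − 0.15 × 10 = 5.5 points between schools. The SD goes from 5.3 (A) or 5.5 (B) as planned to 4.8 or 5.0 with spread schools.

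**Step 5: a second variance model.** Let between-school variance be ICC × 0.25 and let zones carry half of it. At ICC 0.05:
- As planned: SE = √(0.0125/3 + 0.2375/300 + 0.25/300) = 0.076.
- With one school per zone (and households stratified): about 0.061.
- Power for 10 points rises from 37% to 50%.

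With the zone share varied from 25% to 75%, the SE falls by 7-21% at ICC 0.02 and by 10-33% at ICC 0.05.

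**Step 6: households.** A random 200 puts 67 ± 7 in each third, since √(200 × 1/3 × 2/3) = 6.7. Even with a between-zone SD of 15 points, stratifying lowers the community SE only from 0.0289 to 0.0275, under 5%.

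**The case against.** The strongest reply is that nothing here is wrong. Simple random sampling with a fresh draw each time is a valid design, the added error averages out over rounds, and stratification is a refinement. That stands, and it limits the point to efficiency. It does not remove the point, because the comparison is made at each survey and few surveys are guaranteed.

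A second reply is that the size depends on unknowns. That also stands. The protocol gives no number of schools, no school locations, no catchments and no PR variation within a sub-county. Table 1 compares districts, and the remark in section 1.3 is background on what school databases allow. Section 6.2 requires residence in the sub-county, not near the school, and section 6.6 treats pupils' homes as something still to be learned. Gaps of 20 points would give much larger effects, but they imply a 40-point range inside one sub-county, for which the documents offer no support.

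A third reply is that the error of a three-school survey is part of what is being tested, and that zones built from a special household census would test a different tool. This is fair against census-based zones. It does not apply to sorting the school list by area, which a routine programme could also do.

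A fourth reply is that the larger weakness is three clusters with no design effect in the power statement. That is so: at ICC 0.05 the school arm's design effect is 1 + 99 × 0.05 = 6.0. It is a separate matter, and spreading the schools recovers only the between-zone part.

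**Conclusion.** The point holds as a low-cost design improvement. Leaving the location of three schools to chance adds avoidable random error to each survey's school-community difference, provided PR varies within the sub-county and pupils mostly live near their school. Under the stated assumptions the SD of the difference falls by about a quarter at 10-point gaps and by under a tenth at 5-point gaps. No precision is lost if zones do not differ.

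Four stronger readings are tempting and are not supported:
- That most surveys will in fact miss a third of the sub-county. The 60-77% depends on hypothetical equal zones, an unstated number of schools and pupils living in their school's zone.
- That the school estimate is biased. The error is chance variation around the right value.
- That the household draw shares the fault. It already covers the area.
- That one difference above 10 points would fail the school method. Section 8.2 rejects the method only if it does not approximate the community survey and attempts to correct systematic bias are also unreliable.

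**What to change.** In sections 6.1 and 6.3, replace the simple random draw by one of two options, renewed for each survey:
- sort the school list by area, for example by existing administrative unit, and draw three schools systematically from a random start; or
- form three zones with about equal numbers of schools and draw one at random from each. If the zones hold unequal numbers of schools, selection probabilities differ and the school estimate should be weighted accordingly.

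Stratifying the 200 households by the same areas is optional and gains little.

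Cost: the numbers of schools, pupils, households and visits do not change. Only households are stated to be mapped, so each school's location must be added to the list. Between-school variance within a zone cannot be estimated from a single survey with one school per zone. State in advance that it will be taken conservatively, as if the schools had been drawn without strata, or estimated from the repeated surveys.

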## 6.4 Screening and enrollment of schoolchildren

Clinical evaluation will be conducted at the participating schools. Assessment for eligibility will be done by the study staff, and interviews will be conducted in the appropriate language with the schoolchildren. During the evaluation process, the study personnel will assess for eligibility criteria through conversations with the student. For children fulfilling the eligibility criteria, the study staff will seek assent from the student to participate in the study (appendix 8). The first 20 children from each of the classes 2-6 (100 total) meeting these eligibility criteria will be enrolled into the study. All enrolled children will have basic socio-demographic data including age, sex, weight, and bed net use collected. Tympanic temperature will be measured and recorded for these children. Each child selected will be asked to provide a finger-prick blood sample for testing for malaria parasitemia using an RDT, preparation of thick and thin malaria blood smears, filter paper blood samples and for hemoglobin estimation. All data will be collected using a hand-held computer (appendix 13).

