| Participants and Sample Size | **Community survey:**  Household survey,:  - randomly sample 200 households per site  - administer a household questionnaire to the head of the household or their designate.  Women’s survey:  - sample all women in the reproductive age group (15 – 49 years) in each selected household.  - administer a women’s questionnaire to all selected women  Clinical survey:  **-** sample all children under fifteen years of age in each selected household  - randomly sample one household member within the age category 15-24 years, 25-34 years, 35-44 years, 45-54 years, and > 55 years.  - collect a fingerprick blood sample from each participant for measurement of hemoglobin, thick and thin blood smear, rapid diagnostic test (RDT) for malaria, and filter paper blood sample  **School survey:**  - randomly select 3 primary schools per site.  - randomly select 100 pupils per school (30 children from each of the classes 2-6) |

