# 4.0 STUDY METHODS

## 4.1 Overall study design

We propose to conduct cross-sectional surveys in communities and primary schools twice a year for at least 2 years in the 3 different sites. The surveys will be timed to correspond to the high and low malaria transmission seasons, when possible. In the community surveys, 200 households will be recruited from a list randomly generated from a census database at each site. The community surveys will consist of three components: (1) a household survey targeting heads of households, (2) a women’s survey targeting all women of child-bearing age (15-49 years), and (3) clinical surveys of all children under fifteen years of age, and of one household member within the age category 15-24 years, 25-34 years, 35-44 years, 45-54 years, and > 55 years. The clinical surveys will include a fingerprick blood sample for measurement of hemoglobin, thick and thin blood smear, rapid diagnostic test (RDT) for malaria, and filter paper blood sample. The school surveys will be conducted in 3 randomly selected primary schools per site. A total of 100 randomly selected children will be recruited in each school. The school surveys will include only the clinical assessments including measurement of temperature, and a fingerprick blood sample for measurement of hemoglobin, thick and thin blood smear, RDT for malaria, and filter paper blood sample.

##

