# 9.0 DATA MANAGEMENT

All data will be collected by survey teams using hand-held computers (tablets). Prior to conducting the surveys information from the questionnaires and fields for entering results of biomarker testing will be programmed into the hand-held computers. Programming will include range checks, structure checks and internal consistency checks. Before leaving the household or schools, an inventory will be made of the completed questionnaires and blood samples collected; both will be checked to make sure they are labelled correctly. The completed questionnaires will be checked for mistakes and completeness. Where eligible respondents are absent from the home or school, a minimum of three additional call back visits will be made on different days. Data from these devices will be transferred at the end of every day to our data core facility in Kampala and stored on a secure server. The data file will be kept on a separate network so that only authorized survey staff will have access to the data during collection and processing phase. The file with data from the questionnaires will be merged with results from reading the malaria slides at the laboratory, using the unique bar codes. All filter paper samples and blood slides will be returned to UMSP offices in Kampala.

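### Section 6.4 enrols the first 20 eligible pupils of 30 per class without fixing the order or linking it to the call-back rule, which leaves an avoidable risk of selection bias in the school sample

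*Protocol*

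**What the plan says.** Selection in schools has two steps. Section 6.3 takes the random step: "A random sample of 150 children aged 6-15 years will be selected from each school using the school register", and "Thirty children will be randomly selected from each of the classes 2-6 in the selected schools to participate in the study". Section 6.4 takes the second step at the school: "The first 20 children from each of the classes 2-6 (100 total) meeting these eligibility criteria will be enrolled into the study". Eligibility is settled there by talking with the pupil, and the pupil's assent, which section 6.2 lists as an inclusion criterion, is sought at the same time. No order for working through the 30 is given.

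Three other places bear on this:

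- Section 4.1 describes the result as a random sample: "A total of 100 randomly selected children will be recruited in each school".
- The Study Summary has "randomly select 100 pupils per school (30 children from each of the classes 2-6"), although 30 from each of five classes makes 150.
- Section 9.0 extends the call-back rule to schools: "Where eligible respondents are absent from the home or school, a minimum of three additional call back visits will be made on different days". Section 6.4 mentions no call-back.

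For households, by contrast, section 5.1.1 has staff take the addresses one after another as they stand on the randomly generated list, and return at least three more times when residents are out.

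Section 8.2 bases the school PR on "cross-sectional surveys of 300 children (3 schools x 100 children per school) aged 6-14 years from the primary school surveys" and compares it with the community PR, with a 10-point absolute difference as the yardstick.

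**The concern.** A random draw of 30 stays random only if the 20 who are used are taken from it in an order unrelated to the outcome. If *first* means first to present and qualify on the survey day, the order depends on attendance and on how soon a pupil is screened. Pupils who are absent through illness or who live far away may plausibly differ in PR and anemia. They would drop out once the quota is full.

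Objective 2 compares school estimates with the community survey as the reference, and the end of section 8.2 uses such comparisons to decide whether a streamlined method can substitute for its reference. If the community survey pursues absentees and the school survey fills its quota from those present, part of any gap would come from the enrolment rule but be read as a property of school sampling. Section 6.6 maps a subsample of the surveyed pupils to describe where pupils live, so selection related to distance would also affect that output.

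**Working it through.** **Counts.** Drawn: 5 classes × 30 = 150 per school (6.3). Enrolled: 5 × 20 = 100 per school (6.4). Per site: 3 × 100 = 300 (8.2). The Study Summary gives 100 as the total but 30 as the class number, and these do not agree.

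**The plan's own figure.** Section 8.2 states 80% power with 300 children per method, one-sided 0.05, a 10-point difference and community PR of 20–80%. Treating the two surveys as independent samples with equal true PR p:

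power = Φ(0.10/SE − 1.645), SE = √(2p(1 − p)/300)

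- PR 20% or 80%: 92.2%
- PR 30% or 70%: 84.8%
- PR 40% or 60%: 80.4%
- PR 50%: SE = 0.0408, 0.10/0.0408 − 1.645 = 0.80, power 78.9%

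The required n peaks at 310 at PR 50%, so the stated 80% reproduces to within rounding. This check ignores clustering within schools.

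**Bias from the quota.** Let E be the number of the 30 who are eligible and consenting, including any who would qualify once reached. Then

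PR of all E = (20/E) × PR enrolled + ((E − 20)/E) × PR not enrolled,

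so bias = PR enrolled − PR of all E = ((E − 20)/E) × (PR enrolled − PR not enrolled).

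The protocol gives neither E nor the gap. Both are assumed here. Bias in percentage points:

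| E | share left out | gap 5 | gap 10 | gap 20 |
|---|---|---|---|---|
| 20 | 0 | 0 | 0 | 0 |
| 25 | 5/25 = 0.20 | 1.0 | 2.0 | 4.0 |
| 30 | 10/30 = 0.333 | 1.7 | 3.3 | 6.7 |

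Using up the whole 10 points at E = 30 would take a gap of 10/0.333 = 30 points.

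**Effect on the comparison.** Suppose the true PRs are equal and the enrolment rule makes the school PR too low by b. The chance of showing a difference below 10 points is Φ((0.10 − b)/SE − 1.645), with SE = √(p(1 − p)/300 + (p − b)(1 − p + b)/300):

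| Community PR | b = 0 | b = 1.7 points | b = 3.3 points |
|---|---|---|---|
| 20% | 92.2% | 82.6% | 68.3% |
| 50% | 78.9% | 65.1% | 49.9% |
| 80% | 92.2% | 80.5% | 63.7% |

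A bias well inside the 10 points therefore costs a good deal of the planned power, if it occurs.

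**The case against.** The other side has several good arguments.

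- **Order.** A reader might infer that section 6.4 prescribes a first-come sample. It does not say so. If the 30 are worked in random-list order, as households are, the 20 are a random sample of eligible, consenting pupils and section 4.1 stands. But section 5.1.1 states the order and sections 6.3 and 6.4 do not. Moreover, a pupil who is away cannot be found eligible or give assent that day, so even list order passes over absentees unless call-backs come before replacement.
- **Call-backs.** A reader might infer that sections 6.4 and 9.0 contradict each other. They do not: section 9.0 already covers schools, and section 6.4 nowhere says that absentees are dropped. The two rules are simply not reconciled.
- **Consent.** Early parental consent is a weak route to bias, because section 6.3 provides: "Those parents who do not attend the school meetings will be visited at home and the consent will be sought from their homes". This stands.
- **Reserve.** Drawing 30 to obtain 20 is a sensible allowance for ineligibility and refusal. This stands too, and it makes one third a maximum share left out, not a fixed one.
- **Community losses.** The community survey also has non-response: section 5.3.2 requires presence the night before and excludes people who cannot be located. So it cannot be said that only the school survey is exposed.
- **Planned bias modelling.** Section 8.2 will look for systematic over- or underestimation and adjust by regression. Objective 2 also evaluates the school survey as it is operated. That can deal with a stable bias. Attendance varies from day to day, however, and section 6.1 redraws the schools each round. Section 6.4 asks for no record of why pupils were not enrolled, so this component could not be separated from real school–community differences.

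**Conclusion.** The point holds as an undefined enrolment order that is not reconciled with the call-back rule. On its natural reading, section 6.4 favours pupils who are present and screened early, and the 100 enrolled may then not be the random sample of section 4.1. The result is an avoidable risk of selection bias in the school PR and anemia prevalence, and so in the objective 2 comparison.

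The documents do not show that bias occurs. It needs more than 20 eligible, consenting pupils per class and a PR that differs by presence or screening order. The protocol gives no absence rate, no gap and no direction. For an assumed 10-point gap the bias runs from 0 (E = 20) through 2.0 (E = 25) to 3.3 points (E = 30, the maximum), against the 10-point difference in section 8.2. The change is worth making because it is cheap and the later modelling cannot reliably undo the problem.

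**What to change.** In section 6.4, define the order and link it to section 9.0:

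1. When the register sample is drawn, place the 30 pupils of each class in computer-random order.
2. Enrol in that order until 20 are reached.
3. Pass to the next pupil only when one is ineligible, refuses, or is still absent after the section 9.0 call-backs.
4. Record the reason for each pupil skipped.

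Also align the Study Summary with sections 6.3 and 6.4: 30 drawn and 20 enrolled per class, 150 drawn and 100 enrolled per school.

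The sample stays at 20 × 5 × 3 = 300 per site, so the power figures without bias are unchanged and the quota itself adds no expected bias. The cost is in fieldwork. Section 9.0 already promises the return visits, but making replacement wait for them adds some delay: a pupil who is absent throughout takes the first visit plus at least three more, on different days.
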